#### Email With Information

The TL-I group will receive a weekly email from the investigator that contains additional information about the self-help book or the study. A frequently-asked-questions (FAQs) format will be used for this email (eg, “Q: How can I find the time to practice the recommended exercises?” “A: Select a good moment in your daytime routine, so that practicing the exercises can become a habit. For example, during lunch time, directly after work or half an hour before bed time.”). The information emails will be a work-in-progress during the study because FAQs by participants in the TL-E group will also be integrated into the information emails. Participants will be instructed to read the weekly emails and not to respond to the investigator.

#### Control group

Participants in the control group will be on a waiting list for the first 6 months of the study and will receive the self-help book after they complete the 6-month follow-up assessment. For the sake of comparison at the long-term follow-up, the control group will also receive the information emails in the same way provided in the TL-I group.

### Measures

For a brief overview of all outcome measures and assessment times, see Table 2. Because one of our aims is to examine the working mechanisms underlying the intervention, which requires assessing all included positive psychology components, measures are selected on brevity and availability in the Dutch language.

**Table 2 table2:** Intended questionnaires and assessment times.

			T0	T1	T2	T3
Questionnaire	Measurement	Screening	Pre-test	Post-test	Follow-up^a^	Follow-up^b^
MHC-SF	Well-being/ flourishing	X	X	X	X	X
FS	Social-psychological well-being		X	X	X	X
HADS	Symptoms of depression and anxiety	X			X	X
m-DES	Positive and negative emotions		X	X	X	X^d^
SUS	Use of strengths		X	X	X	X^d^
LOT-R	Optimism		X	X	X	X^d^
SCS-SF	Self-compassion		X	X	X	X^d^
BRS	Resilience		X	X	X	X^d^
SPR	Positive relations		X	X	X	X^d^
EPQ-RSS	Extraversion and neuroticism		X			
NEO-FFI	Conscientiousness		X			
MCQ	Direct medical consumption costs		X	X^c^	X^c^	X
PCQ	Non-medical productivity costs		X			X
Brugha Life-events	Positive and negative life-events		X	X	X	X
CSQ-8	Client satisfaction			X^d^		
Process evaluation	Invested time, adherence, positive changes			X^d^		X^e^
	Level of (continued) use					X
Demographics	Gender, age, education, marital status, living situation, ethnicity, daily activities	X				

^a^ 6 months after T0.

^b^ 12 months after T0.

^c^ Only medical health care costs are assessed, not medication costs.

^d^ Only assessed in the experimental groups, not the control group.

^e^ Only assessed in the control group, not the experimental groups.

#### Primary Outcome

Well-being is the primary outcome of this study, measured with the 14-item MHC-SF and the 8-item Flourishing Scale (FS). The items of the MHC-SF can be divided into 3 subscales: emotional well-being (3 items), social well-being (5 items), and psychological well-being (6 items). All items can be answered on a 6-point answer scale from 0 (never) to 5 (almost always). A mean score will be computed separately for the total scale and the 3 subscales. The MHC-SF has excellent psychometric properties [5,13]. The FS measures social-psychological well-being with 8 positively formulated items. Participants rate the items on a 7-point scale from 1 (strongly disagree) to 7 (strongly agree). Total summed scores can range from 8-56. The FS has demonstrated good internal consistency and construct validity [69].

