**Results:**

The primary outcomes are well-being and flourishing (ie, high levels of well-being). Secondary outcomes are the well-being components included in the intervention: positive emotion, use of strengths, optimism, self-compassion, resilience, and positive relations. Other measures include depressive and anxiety symptoms, personality traits, direct medical and non-medical costs, life-events, and client satisfaction.

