#### Secondary Outcomes

The MHC-SF is also used to measure the amount of flourishing [13,43]. Flourishers score 4 or 5 on 1 or more items on the emotional well-being subscale in combination with a score of 4 or 5 on 6 of the 11 remaining items. Languishers are those with scores of 0 or 1 on these subscales, and individuals who are neither flourishing nor languishing are labelled as moderately mentally healthy.

Depressive and anxiety symptoms will be measured with the HADS [44]. Each subscale consists of 7 items, 14 items in total. Answer categories differ per item, but all items have 4 answer categories with scores ranging from 0-3. Item scores are summed into a total scale score for anxiety (range 0-21) and depression (range 0-21). The HADS is a widely validated instrument and can be used as a screening instrument in different populations [70,71]. A cut-off score of 10 and above on each subscale is generally used to identify individuals with at least mild depressive or anxiety symptomatology [44,70].

Positive and negative emotional states will be assessed with the modified Differential Emotions Scale (m-DES), which measures 8 groups of positive emotions and 8 groups of negative emotions on a 7-point scale (1 = not at all, 7 = very intense). Total mean scores will be computed. Although the DES is validated and widely used, the m-DES has not yet been validated [72].

The Strength Use Scale (SUS) is a 14-item scale to assess participants’ use of their strengths in a variety of settings [73]. Scores range from 1 (strongly disagree) to 7 (strongly agree) with a total summed score of 14 to 98. The SUS possesses high internal consistency and long-term stability [74].

Optimism will be assessed with the 10-item Life Orientation Test-Revised (LOT-R) [75,76]. Items are rated on a 5-point scale ranging from 0 (strongly disagree) to 4 (strongly agree) and indicate participants’ evaluation of positive expectations about the future. There are 4 filler items which are excluded from analysis. Scores on the 6 items are summed into a total optimism score ranging from 0-24. The LOT-R has shown predictive and discriminant validity [75].

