### Statistical Analyses

The Consolidated Standards of Reporting Trials (CONSORT) statement [91] will be used to report the results. Independent *t* tests and Chi-square statistics (X^2^) will be used to examine baseline differences between the study groups. Non-significant socio-demographic differences at baseline will indicate successful randomization. Internal consistency of the constructs will be determined using Cronbach’s alpha. To examine the efficacy of the intervention, intention-to-treat analyses will be conducted by including all participants in the analyses who have been randomized. The Expectation Maximization (EM) method will be used to impute all missing data on the continuous measures of T1, T2 and T3. This method imputes the data by maximum likelihood estimation using the observed data in an iterative process [92]. The intention-to-treat analysis will be compared with a completers-only analysis.

To examine significant differences between the 3 groups, we will perform repeated measures ANOVA in a 3 (group) x 3 (time) design with well-being (MHC-SF and FS) as the primary dependent variable and positive/negative emotions (mDES), the use of strengths (SUS), optimism (LOT-R), self-compassion (SCS-SF), resilience (BRS), and positive relations with others (SPR) as the secondary dependent variables. Significant time x group interactions will be tested with Tukey’ post hoc tests. Within-group effects (Cohen’s *d*) will be calculated by subtracting the mean post-test or follow-up score from the mean baseline score and dividing the difference by the pooled standard deviation. Between-group effects (Cohen’s *d*) will be calculated by subtracting the mean post-test or follow-up score of the experimental group from the mean post-test or follow-up score of the control group, and dividing the difference by the pooled standard deviation [93]. These effect sizes are used to gain insight into the relevance of the significant effects. To examine changes in the amount of flourishers, languishers, and moderately mentally healthy (MHC-SF), descriptive statistics will be used. Changes in categories will be tested with X^2^-statistics.

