Mediator and moderator analyses will be performed as described by Hayes [94,95]. Mediator analyses will be conducted to investigate which of the specific components of the intervention—positive emotion, use of strengths, optimism, self-compassion, resilience, and positive relations—contribute to its efficacy and mediate overall well-being. Moderator analyses will be conducted to examine which specific subgroups will improve most (or least) on well-being and flourishing from participation in one of the experimental groups. The independent variables of gender, educational level, life-events, personality traits, level of adherence to the intervention, and participation satisfaction will be entered as moderators in regression analyses.

A cost-effectiveness analysis will be conducted from a societal perspective. For each condition, the mean annual health care costs (MCQ), costs due to productivity losses (PCQ), and intervention costs will be calculated on an annual per capita basis for the reference year 2014. All costs will be expressed in Euro (€). The incremental cost-effectiveness ratio (ICER) will be calculated using a bootstrap approach. Then, a cost-effectiveness acceptability curve will demonstrate the probability of the cost-effectiveness of TL-E and TL-I compared to WL, for a range of willingness-to-pay (WTP) ceilings. All tests will be two-sided and will use alphas of 0.05. All data-analyses will be performed with SPSS version 21.0 or higher.

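### The primary outcome is not fixed: the Abstract counts flourishing as primary, the Methods count it as secondary, and the Methods' own primary outcome is two scales each tested at 5% with no rule linking them

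*Protocol article*

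**What the plan says.** On which outcome is primary, two current parts of the article disagree.

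- Abstract, Results: "The primary outcomes are well-being and flourishing (ie, high levels of well-being"). The same paragraph says "Secondary outcomes are the well-being components included in the intervention", and flourishing is not among them.
- Methods, Primary Outcome: "Well-being is the primary outcome of this study, measured with the 14-item MHC-SF and the 8-item Flourishing Scale (FS"). The MHC-SF total is a mean of items scored 0 to 5. The FS is a sum from 8 to 56.
- Methods, Secondary Outcomes opens with flourishing: "The MHC-SF is also used to measure the amount of flourishing".

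On the analysis, Statistical Analyses plans a "repeated measures ANOVA in a 3 (group) x 3 (time) design with well-being (MHC-SF and FS) as the primary dependent variable". Tukey post hoc tests follow a significant time-by-group interaction. For the flourishing categories, "Changes in categories will be tested with" chi-square statistics, next to descriptive counts. The section ends with a general rule: "All tests will be two-sided and will use alphas of 0.05".

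Sample Size powers the trial on well-being at a standardized effect of 0.40, two-tailed 5% and 80% power. It gives 99 per group, or 132 per group and 396 in total after 25% dropout. It does not say which scale this refers to.

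**The concern.** Two gaps combine. First, a reader of the Abstract and a reader of the Methods would judge the trial on different outcomes. A later analysis plan can choose between the two statements but cannot make both true.

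Second, even if the Methods govern, well-being is two variables. Statistical Analyses speaks of one dependent variable but defines no composite. The natural reading is therefore one ANOVA per scale, each at 0.05. Tukey adjusts across the three groups, not across the two scales. If the MHC-SF and the FS disagree, the plan does not say whether the trial succeeded, and that choice could be made after the results are seen. At stake is whether the stated 5% error rate and 80% power describe the trial's main conclusion.

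**Working it through.** **Inputs from the article.** d = 0.40, two-sided alpha 0.05, power 0.80, 25% dropout, three groups 1:1:1 (Sample Size, Randomization); two primary scales and a 3 x 3 repeated measures ANOVA (Statistical Analyses).

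**Assumptions.** The correlation r between the scales is not given, so 0.5 to 0.8 is used. For joint power, d = 0.40 is taken on each scale.

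**1. The plan's own figure.** n = 2(z₀.₉₇₅ + z₀.₈₀)² / d² = 2(1.960 + 0.842)² / 0.16 = 98.1, so 99 per group. Then 99 / (1 − 0.25) = 132, 3 × 99 = 297 and 3 × 132 = 396. Power at 99 per group is 0.804 by the normal approximation (0.800 by the t distribution). All stated figures reproduce, for one comparison of two groups on one endpoint at 5%.

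**2. If either scale suffices.** For two single contrasts, the chance of at least one false positive is 1 − P(|Z₁| < 1.96 and |Z₂| < 1.96), with (Z₁, Z₂) bivariate normal and correlation r. Independence would give 1 − 0.95² = 0.0975.

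The plan's first test is a group-by-time interaction, not a single contrast. That test was therefore also simulated with no true group differences, for 99 per arm and an assumed correlation of 0.6 between time points within a person.

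| r between scales | Two single tests | At least one significant interaction |
|---|---|---|
| 0.5 | 9.1% | 9.0% |
| 0.7 | 8.3% | 8.7% |
| 0.8 | 7.8% | 8.1% |

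With 132 per arm, the simulated interaction figure runs from 8.0 to 9.2% over the same correlations. Both routes give about 8 to 9%.

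**3. If both scales must succeed.** The level stays at or below 5%. Per scale, the mean of the test statistic is 0.40 / √(2/99) = 2.814, and 2.814 − 1.960 = 0.854, so power is Φ(0.854) = 0.804. Joint power is the bivariate normal probability Φ₂(0.854, 0.854; r):

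| r between scales | Joint power at 99 per group |
|---|---|
| 0.5 | 0.692 |
| 0.7 | 0.717 |
| 0.8 | 0.733 |

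This uses the pairwise comparison on which the sample size rests.

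**4. Consequence.** One reading of the primary outcome loses the stated 5%, and the other loses the stated 80%. Only a single lead scale keeps both.

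**The case against.** The best defence is that the Methods agree with themselves. Primary Outcome, Sample Size and Statistical Analyses all treat well-being as primary, and flourishing stands under Secondary Outcomes. The contradiction is then one sentence of the Abstract. That is fair, and it is why the correction should go to the Abstract. It does not settle which of the two scales decides.

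A second defence is that the Tukey contrasts are run only after a significant interaction. In a simulation of this sequence with no true differences (132 per arm, same assumed correlations), any significant contrast on either scale at post-test or 6 months occurred in 2.1 to 2.6% of trials. This stands for claims resting on a contrast when neither book arm works. It does not cover a claim based on the interaction itself. Nor does it cover the case where one book arm works: the interaction then tends to be significant, and the contrasts for the other arm lose that protection.

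Stronger readings are tempting but not supported:

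- **A larger error rate from counting time points as separate tests.** The interaction test spans the time points, so the plan does not work that way.
- **A larger error rate from adding flourishing as a third primary test.** This applies only if the Abstract governs.
- **A flourishing test restricted to completers.** One might infer this because EM imputation is stated for continuous measures. But the plan includes all randomised participants, uses completers only for comparison, and imputes the MHC-SF, from which the categories could be derived.
- **An invalid chi-square because it ignores baseline.** An unadjusted comparison of randomised arms is valid.

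**Conclusion.** The point holds in two parts. The Abstract and the Methods contradict each other on whether flourishing is primary. The Methods' primary outcome is two separately scored scales at 0.05 each, with no lead scale and no either/both rule.

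Its size depends on the missing rule. If either scale suffices, the chance of at least one false-positive interaction is about 8 to 9% instead of 5%. If both must succeed, joint power is about 0.69 to 0.73 instead of 0.80. These figures rest on assumed correlations of 0.5 to 0.8 between the scales and, for power, on d = 0.40 on each. A correlation outside that range would move them, but the missing rule would remain.

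The sample size arithmetic is correct. No fault is found in the flourishing test as such.

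**What to change.** 1. Name one primary scale in Primary Outcome, Sample Size and Statistical Analyses. The MHC-SF total mean score is one candidate, although Sample Size does not say which scale was used for power.
2. Test the other scale next in fixed sequence: at two-sided 0.05, and confirmatory only if the first is significant. This keeps the error rate across the two scales at 5%.
3. Correct the Abstract so that well-being is the primary outcome and flourishing is secondary, in line with the Methods.

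The change is one of wording, and 99, 132 and 396 stay as they are. The downside, with the MHC-SF leading, is that a result on the FS alone can no longer carry the primary claim. The alternative of allowing success on either scale at 0.025 each would need 119 per group by the normal approximation. That is 119 / 0.75, or 159 after dropout, and 477 in total. At 99 per group, power per scale would fall to about 0.72.

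A baseline-adjusted logistic model for flourishing would be an optional improvement. It is not needed to correct this point.

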#### Secondary Outcomes

The MHC-SF is also used to measure the amount of flourishing [13,43]. Flourishers score 4 or 5 on 1 or more items on the emotional well-being subscale in combination with a score of 4 or 5 on 6 of the 11 remaining items. Languishers are those with scores of 0 or 1 on these subscales, and individuals who are neither flourishing nor languishing are labelled as moderately mentally healthy.

Depressive and anxiety symptoms will be measured with the HADS [44]. Each subscale consists of 7 items, 14 items in total. Answer categories differ per item, but all items have 4 answer categories with scores ranging from 0-3. Item scores are summed into a total scale score for anxiety (range 0-21) and depression (range 0-21). The HADS is a widely validated instrument and can be used as a screening instrument in different populations [70,71]. A cut-off score of 10 and above on each subscale is generally used to identify individuals with at least mild depressive or anxiety symptomatology [44,70].

Positive and negative emotional states will be assessed with the modified Differential Emotions Scale (m-DES), which measures 8 groups of positive emotions and 8 groups of negative emotions on a 7-point scale (1 = not at all, 7 = very intense). Total mean scores will be computed. Although the DES is validated and widely used, the m-DES has not yet been validated [72].

The Strength Use Scale (SUS) is a 14-item scale to assess participants’ use of their strengths in a variety of settings [73]. Scores range from 1 (strongly disagree) to 7 (strongly agree) with a total summed score of 14 to 98. The SUS possesses high internal consistency and long-term stability [74].

Optimism will be assessed with the 10-item Life Orientation Test-Revised (LOT-R) [75,76]. Items are rated on a 5-point scale ranging from 0 (strongly disagree) to 4 (strongly agree) and indicate participants’ evaluation of positive expectations about the future. There are 4 filler items which are excluded from analysis. Scores on the 6 items are summed into a total optimism score ranging from 0-24. The LOT-R has shown predictive and discriminant validity [75].

Self-compassion will be assessed with the Self-Compassion Scale-Short Form (SCS-SF), which consists of 12 items. Participants rate the items on a 7-point scale ranging from 1 (rarely or never) to 7 (almost always) with a total summed score ranging from 12-84. The SCS-SF has proven to be a valid equivalent of the long-form version [77] developed by Neff [78].

The 6-item Brief Resilience Scale (BRS) [79] will be used to evaluate the level of resilience, which is the ability to bounce back and cope with stress or negative life-events. Items are rated on a 5-point scale from 1 (strongly disagree) to 5 (strongly agree) with total mean scores ranging from 1 to 5. The psychometric properties are good [79].

Although positive relations will be assessed with 1 item of Ryff’s scales of psychological well-being [19] in the MHC-SF, we will also measure the original Subscale of Positive Relations (SPR) as proposed by Ryff [19]. This subscale contains 9 items and a 6-point scale ranging from 1 (strongly disagree) to 6 (strongly agree) [80] and a total summed score that range of 9-54.

#### Tertiary Outcomes

The personality traits extraversion and neuroticism will be assessed with the Eysenck Personality Questionnaire-Revised Short Scale (EPQ-RSS) [81-83] and conscientiousness with the NEO Five Factor Inventory (NEO-FFI) [84]. These personality surveys are widely used and validated. Direct medical and non-medical costs will be measured with the Dutch Medical Consumption Questionnaire (MCQ) [85] and 5 items from the Productivity Cost Questionnaire (PCQ) [86]. Other variables that will be assessed are positive and negative life-events with a scale based on the Brugha Life-events section [87], and the socio-demographics of gender, age, educational, marital status, living situation, ethnicity, and daily activities.

#### Process Outcomes

The Client Satisfaction Questionnaire-short form (CSQ-8) [88,89] will be used to determine overall satisfaction. Additional questions will be asked about time spent with the intervention and self-help book modules, adherence to each module, and significant positive changes since they started with the intervention. The latter question is based on the Client Change Interview Protocol [90]. All email correspondence between participants and personal counselors will be retrieved and saved for content analysis.

### Sample Size

Well-being is the primary outcome used for the power calculation. We expect to detect a significant effect on well-being between the experimental groups TL-E and TL-I compared to the WL group. Based on recent meta-analyses [17,18] and a previous comparable study [38], we expect to find a standardized effect size on well-being of 0.40 or larger. The targeted sample size is 99 participants per group (297 in total) to provide a statistical power of (1 - *β*) = 80% and a 5% significance level (two-tailed). To allow a study dropout rate of 25%, we need 132 participants in each condition and 396 participants in total for the trial.

### Statistical Analyses

The Consolidated Standards of Reporting Trials (CONSORT) statement [91] will be used to report the results. Independent *t* tests and Chi-square statistics (X^2^) will be used to examine baseline differences between the study groups. Non-significant socio-demographic differences at baseline will indicate successful randomization. Internal consistency of the constructs will be determined using Cronbach’s alpha. To examine the efficacy of the intervention, intention-to-treat analyses will be conducted by including all participants in the analyses who have been randomized. The Expectation Maximization (EM) method will be used to impute all missing data on the continuous measures of T1, T2 and T3. This method imputes the data by maximum likelihood estimation using the observed data in an iterative process [92]. The intention-to-treat analysis will be compared with a completers-only analysis.

To examine significant differences between the 3 groups, we will perform repeated measures ANOVA in a 3 (group) x 3 (time) design with well-being (MHC-SF and FS) as the primary dependent variable and positive/negative emotions (mDES), the use of strengths (SUS), optimism (LOT-R), self-compassion (SCS-SF), resilience (BRS), and positive relations with others (SPR) as the secondary dependent variables. Significant time x group interactions will be tested with Tukey’ post hoc tests. Within-group effects (Cohen’s *d*) will be calculated by subtracting the mean post-test or follow-up score from the mean baseline score and dividing the difference by the pooled standard deviation. Between-group effects (Cohen’s *d*) will be calculated by subtracting the mean post-test or follow-up score of the experimental group from the mean post-test or follow-up score of the control group, and dividing the difference by the pooled standard deviation [93]. These effect sizes are used to gain insight into the relevance of the significant effects. To examine changes in the amount of flourishers, languishers, and moderately mentally healthy (MHC-SF), descriptive statistics will be used. Changes in categories will be tested with X^2^-statistics.

Mediator and moderator analyses will be performed as described by Hayes [94,95]. Mediator analyses will be conducted to investigate which of the specific components of the intervention—positive emotion, use of strengths, optimism, self-compassion, resilience, and positive relations—contribute to its efficacy and mediate overall well-being. Moderator analyses will be conducted to examine which specific subgroups will improve most (or least) on well-being and flourishing from participation in one of the experimental groups. The independent variables of gender, educational level, life-events, personality traits, level of adherence to the intervention, and participation satisfaction will be entered as moderators in regression analyses.

A cost-effectiveness analysis will be conducted from a societal perspective. For each condition, the mean annual health care costs (MCQ), costs due to productivity losses (PCQ), and intervention costs will be calculated on an annual per capita basis for the reference year 2014. All costs will be expressed in Euro (€). The incremental cost-effectiveness ratio (ICER) will be calculated using a bootstrap approach. Then, a cost-effectiveness acceptability curve will demonstrate the probability of the cost-effectiveness of TL-E and TL-I compared to WL, for a range of willingness-to-pay (WTP) ceilings. All tests will be two-sided and will use alphas of 0.05. All data-analyses will be performed with SPSS version 21.0 or higher.

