### Randomization

Randomization will be conducted after all eligible participants complete the baseline questionnaire, with 396 participants being randomly assigned to 1 of the 3 groups (allocation ratio, 1:1:1). Randomization will be stratified by gender and educational level (ie, low, medium, high) using a computerized random number generator created with Excel. This is an automated process with no interference from the investigators.

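### Non-significant baseline tests cannot show that randomisation succeeded; a sound allocation would still give at least one p<0.05 in about 23% to 28% of trials on the likely readings

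*Protocol article*

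**What the plan says.** The Randomization section of the protocol article describes 1:1:1 allocation of 396 participants to three groups by a computerised random number generator, after the baseline questionnaire is complete. It adds that "This is an automated process with no interference from the investigators" and that "Randomization will be stratified by gender and educational level".

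The Statistical Analyses section states that independent t tests and chi-square statistics "will be used to examine baseline differences between the study groups". The next sentence sets out how to read them: "Non-significant socio-demographic differences at baseline will indicate successful randomization". The same section closes with "All tests will be two-sided and will use alphas of 0.05". No multiplicity allowance is given for the baseline tests, and nothing says what follows if one of them is significant.

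The socio-demographics are listed under Tertiary Outcomes as "gender, age, educational, marital status, living situation, ethnicity, and daily activities". That makes seven, of which gender and education are stratification factors and five are not.

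Efficacy is analysed by a 3 (group) by 3 (time) repeated measures ANOVA with no covariates named. Between-group Cohen's d is the difference in post-test or follow-up means divided by the pooled standard deviation, and it is used to judge the relevance of significant effects.

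**The concern.** A baseline significance test asks whether an observed difference could be chance. Under automated random allocation the answer is already known: it is chance. The null hypothesis of each test is true by design, so a significant result is a false alarm at the nominal rate. A non-significant result shows neither that the allocation was sound nor that the arms are alike.

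Gender and education add almost nothing as evidence, because the Discussion itself expects stratification to equalise them across groups. The rule therefore rests on five other variables. It does not cover T0 well-being, which is not a socio-demographic and is likely to bear more closely on the outcome.

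Two things are at stake. The report could make a wrong statement about randomisation in either direction. In addition, a chance T0 difference would pass uncorrected into the between-group Cohen's d while the trial is described as successfully randomised.

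**Working it through.** **The plan's own figure.** The article gives no error rate for the baseline rule. The figure it does give, and which fixes the arm size used here, is the sample size. With d = 0.40, 80% power and a two-sided 5% level, the t-based requirement is 99.08 per group and the normal-approximation power at 99 is 80.4%. Inflating, 99/0.75 = 132 per group and 3 × 132 = 396. The plan's numbers reproduce. Because the baseline questionnaire precedes randomisation, 132 per arm is also the right size for baseline comparisons.

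**Inputs for the rule.**
- Level per test: 0.05, two-sided (Statistical Analyses).
- Groups: three, so three pairwise comparisons per variable where a two-group test is used (Randomization).
- Variables: 7 listed − 2 stratified = 5 (age, marital status, living situation, ethnicity, daily activities).
- Assumptions: the five variables are independent, and any single p<0.05 counts as a failure of the rule. The article states neither.

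**One three-group test per variable.**
1 − 0.95^5 = 1 − 0.774 = 22.6%.

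**Pairwise testing of one variable.** Simulating 20,000 trials with three arms of 132 and no true difference, the chance of at least one p<0.05 among the three t tests is 12.1%.

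**Age by three pairwise t tests, the other four by one chi-square test each.** The article names t tests, which compare two groups, and chi-square tests, which can take all three at once. Age is the one naturally continuous variable of the five.
1 − 0.879 × 0.95^4 = 1 − 0.879 × 0.8145 = 28%.

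**All five variables tested pairwise.**
1 − (1 − 0.1215)^5 = 47.7%, about 48%.

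**Sensitivity to correlation.** In a further simulation, age was continuous, the other variables were categorical with assumed category proportions, and the latent correlation ran from 0 to 0.7. It gave 20–23% with three-group tests and 43–48% with pairwise tests. Correlation lowers the figures slightly.

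**Where T0 enters.** The article does not name the three time points of the ANOVA. The control group waits until the 6-month assessment and then receives the book (Control group section), so T0, T1 and T2 is the natural reading. On that reading the time by group interaction compares changes that include T0. The between-group Cohen's d does not: it uses post-test or follow-up means alone. A chance T0 difference therefore enters d in proportion to the correlation between T0 and the later score, which the article does not give.

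**The case against.** The strongest defence is that nothing hangs on the sentence. It runs in one direction only, names no response to a significant result, selects no covariates and leaves the efficacy analysis unchanged. This stands, and it limits the consequence. A reader might infer that a significant test would lead to randomisation being declared failed, or to covariates being chosen by p-value. The article plans neither.

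A reader might also infer that the rule would misfire about half the time. That needs three pairwise tests on four variables that are naturally categorical, for which one chi-square test covers all three arms. The 48% is an upper bound under one way of testing, not the expected rate. Counting all seven socio-demographics would raise the rates further, but it treats gender and education as free to vary when the design balances them.

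A third tempting step is to note that a difference of up to 1.96 × √(2/132) = 0.24 SD in a continuous baseline variable stays non-significant, and to set this against the 0.40 SD effect. The two are not comparable. The first is a covariate imbalance and the second an outcome difference, and the link between them is the covariate-outcome correlation, which the article does not give. If it were 0.1 to 0.3 (an assumption), the outcome shift would be 0.24 × 0.1 = 0.02 SD to 0.24 × 0.3 = 0.07 SD.

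Finally, it can be said that baseline well-being is not ignored, since the time by group test most likely contains T0. This stands for the primary test. It does not stand for the between-group Cohen's d.

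**Conclusion.** The rule is wrong as written and should go. With correct random allocation it would be contradicted by at least one p<0.05 in about 23% of trials with three-group tests, about 28% if only age is tested pairwise, and up to about 48% only if every variable is. These figures assume five independent unstratified variables and the implied converse of the rule.

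The documents do not support a claim that the primary test is invalid or that a failed-randomisation decision is planned. The exposure is a statement about randomisation that the data cannot support, and unadjusted between-group effect sizes. The sponsor should make the correction, but the trial's main conclusion does not turn on it.

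**What to change.** 1. Delete the sentence on successful randomisation and the baseline significance tests. Describe baseline characteristics and T0 scores by arm. Evidence that randomisation was sound comes from the account of how the sequence was generated and applied.
2. Pre-specify, whatever imbalance is observed, that the primary analysis adjusts for gender and educational level, as the stratification factors, and for the T0 score of the outcome. An ANCOVA or a mixed model on T1 and T2 would do this.
3. Take the between-group effect sizes from that model instead of from raw post-test or follow-up means.

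Step 1 costs nothing. Steps 2 and 3 go beyond wording, because they replace the stated ANOVA model. The price is some analysis work and a few degrees of freedom: with gender in two levels and education in three, 1 + 2 + 1 = 4 covariate terms among 396 randomised participants. No new data are needed, since the trial already stratifies by or collects all three covariates.
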